
## Design and methods

2

**Study Design:** This study is a single-case experimental design (SCED) carried out in a specialized academic center for child and adolescent psychiatry (Levvel, Amsterdam, The Netherlands). In a SCED, statistical power is generated through frequent and repeated measurements of the primary outcome over time to monitor within-subject changes [22]. This makes a SCED highly suitable for measuring the treatment effect of individualized treatments (such as children with SM). Due to their adaptability and statistical rigor, SCEDs can be used for innovative treatments in order to generate initial evidence before moving on to more traditional group-based designs [22,23]. This study employs a five-phase design: baseline (A: 2 weeks, no treatment), three individualized treatment phases. The first treatment phase (B: protocol step 1–5, treatment) requires the child to respond to the teacher by producing sounds. Treatment phase two requires the child to respond verbally to teacher (C: protocol step 6–10, treatment). During the last phase of the treatment focuses on the intensification of verbal communication to solidify treatment gains (D: training phase, treatment) and follow-up phase (E: 12 weeks, no treatment). Previous research in our center concluded that the average treatment duration is on average 25 weeks (see Fig. 1).

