**Fig. 1 fig1:**
[figure not shown]
Study design.

Experience sampling method (ESM) assessments (see Paragraph 2.3.1 and Appendices A and B) are used to quantify SM symptoms. These assessments are conducted thrice weekly via the M-path smartphone application [24] by parents and teachers. Considering the average treatment length of 25 weeks, yielding approximately 117 time points across all phases. To ensure adherence and feasibility, the study design was developed balancing a valid number of frequent assessments (after consulting a statistics expert, SB) with the burden for participants, based on ample experience of our research group in conducting ESM studies.

ESM measures are supplemented by comprehensive assessments at key time points. The comprehensive assessment consists of a standardized diagnostic measure of the primary outcome (i.e. SM symptoms), secondary outcomes (i.e. emotional and behavioral problems, anxiety, parenting burden, family accommodation and VR evaluation) as well as relevant predictors, covariates, and potential confounding factors (i.e. parental behavioral and emotional problems, parenting style, immersive tendencies and communication). Fig. 1 provides an overview of the study procedures and assessments conducted at each time point.

The baseline assessment [T0] includes both primary and secondary outcomes, and potential confounding factors, as reported by parents, teachers, and children. At the start of each study phase [T1], [T2], and [T3] parents and teachers report on the *primary outcome* only. Post-treatment [T4] and follow-up [T5] assessments are similar to the baseline assessment, measuring only the primary and secondary outcomes across all informants. Due to the individualized treatment approach, clinical assessments are standardized by therapeutic progress rather than chronological time, resulting in variable intervals between assessments across participants.

**Inclusion criteria:** Children are eligible if they attend primary school, are 4–13 years old, and are referred to our center for diagnosis and treatment for SM between January 2025 until December 2026. Psychiatric comorbidity is permitted, as long as SM is the primary treatment target. Medication use is allowed, provided it has been stable for four weeks prior to participation and remains unchanged throughout treatment.

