### Sample size calculation

3.1

To establish the efficacy of a treatment, SCEDs involve the comparison of different treatment phases. For statistical analysis, each phase of the intervention needs at least five to 20 datapoints [34]. The study design has five phases, and it is ensured that each phase of the intervention will have at least five data points. SCED methodology provides substantial within-person statistical power due to the high number of repeated measurements per participant, ensuring that each individual case has sufficient data to detect meaningful within-person changes.

A power analysis was conducted using the Shiny app SCED Power Analysis [47]. A meta-analysis evaluating the efficacy of CBT for SM reported a large effect size (Hedges' adjusted g = 1.00 [0.62–1.39]) [48]. To detect an expected effect size of Cohen's d = 0.8 and an autocorrelation of 0.4, a sample size ranging from four to eight participants should provide sufficient power to establish an effect from baseline to intervention using the Permutation Distance Test [49]. The planned power analysis pertains to the aggregated, group-level effect, which will be estimated through a meta-analytic synthesis of the individual SCED p-values. The target sample size of *N* = 15 participants refers to the number of individual cases contributing to the pooled group effect.

Given that SM often occurs in young children the physical comfort of the headset might be compromised for children with smaller head sizes. To account for potentially higher dropout rates and missing data, our aim is to include 15 participants to ensure sufficient data for analysis.

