#### Primary outcomes

3.1.1

*SCED*: The ESM measure of SM symptoms is used to evaluate the primary outcome. In Single-Case Experimental Designs (SCEDs), visual analysis is the preferred starting point for assessing treatment effects. The ESM data are presented graphically to assess patterns in trend, level, and stability across and within intervention phases [50]. Additionally Tau-U will be reported [51]. Tau-U is a non-parametric effect size that was created for SCEDs reflecting the degree of non-overlap of observations between two phases. By incorporating both level changes and trend adjustments it is possible to control for baseline trends. Tau-U can be used for statistical testing and for meta-analytic purposes to establish a group effect of the intervention [51].

The Permutation Distance Test (PDT) [49] will be used to test the difference in medians between phases within an individual. The PDT tests the null hypothesis that the medians of the different phases are the same, while accounting for autocorrelation of the data.

*Standardized assessment:* To evaluate whether the change in the frequent assessment SM symptoms is reliable across the different study phases, a reliable change index (RCI) [52] will be computed for the SMQ and the Social Context of Speaking questionnaire. These questionnaires serve to validate the results obtained from the frequent measurements. To test for differences on a group level Friedman's analysis of variance (ANOVA) [53] will be used.

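### With 6 baseline reports Tau-U can correct almost none of a baseline trend, and its usual standard error would not suit the plan's own autocorrelation of 0.4

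*Protocol article*

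**What the plan says.** Section 3.1.1 (Primary outcomes) starts the analysis of the frequent parent and teacher reports with visual analysis and adds Tau-U as a non-overlap effect size between two phases. Two properties are claimed for it. On trend: "By incorporating both level changes and trend adjustments it is possible to control for baseline trends". On inference: "Tau-U can be used for statistical testing and for meta-analytic purposes", the latter meaning a group effect. No variance, variant or treatment of autocorrelation is given for Tau-U.

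The same section commits to the PDT as the test between phases within a child, and says that it allows for autocorrelation. Section 3.1 (Sample size calculation) bases power on the PDT, with an expected d of 0.8 "and an autocorrelation of 0.4". It takes the group effect from a synthesis of individual p-values.

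The data available to Tau-U follow from Section 2 (Design and methods): "baseline (A: 2 weeks, no treatment), three individualized treatment phases", then a "follow-up phase (E: 12 weeks, no treatment". Reporting is three times a week: "These assessments are conducted thrice weekly via the M-path smartphone application".

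**The concern.** There is no concurrent control, and treatment averages 25 weeks. A child who is already improving before treatment, for example by settling into a class or maturing, is therefore a direct rival explanation for a phase difference. Tau-U is the only statistical method in the analysis of the frequent measure for which control of baseline trend is claimed. If 6 baseline reports cannot deliver that control, the stated safeguard is nominal, and a reader of the results would trust an adjustment that does almost nothing.

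The second issue is conditional. The plan expects autocorrelated reports and says that Tau-U may be used for testing and pooling. The customary Tau-U standard error treats reports as independent. Used that way, Tau-U would give individual and group p-values that are too small.

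**Working it through.** **Inputs.** From the article: baseline 2 weeks, treatment 25 weeks on average, follow-up 12 weeks, three reports a week, autocorrelation 0.4, at least five reports per phase, 15 children. Assumed, because the article does not state them: two-sided α = 0.05, and an equal split of the treatment reports over phases B, C and D (25 each).

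**1. The plan's own count.** 3 × (2 + 25 + 12) = 117, which matches "Considering the average treatment length of 25 weeks, yielding approximately 117 time points across all phases". It divides into 6 baseline, 75 treatment and 36 follow-up reports per informant.

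**2. Largest possible trend correction.** Tau-U with baseline correction is (S_AB − S_A)/(nA × nB). S_AB counts improving minus worsening pairs between phases, and S_A does the same within baseline. With nA = 6, S_A is at most 6 × 5/2 = 15.

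| Comparison phase | nB | 15/(6 × nB) |
|---|---|---|
| Five-report minimum | 5 | 0.50 |
| One treatment phase (equal split) | 25 | 0.10 |
| B, C and D together | 75 | 0.033 |

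**3. A perfect baseline trend that simply continues.** Every pair improves, so S_AB = nA × nB. The usual standard error of S_AB is √(nA × nB × (nA + nB + 1)/3).
- nB = 25: Tau-U = (150 − 15)/150 = 0.90; z = 135/√1600 = 3.4.
- nB = 75: Tau-U = (450 − 15)/450 = 0.97; z = 435/√12300 = 3.9.
- nB = 5: Tau-U = (30 − 15)/30 = 0.50; z = 15/√120 = 1.4.

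With no treatment effect at all, the corrected statistic is close to its maximum for phases of realistic length.

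**4. Noisy trends, no treatment effect, autocorrelation 0.4 (simulation, 8,000 series).** The trend sizes are illustrative, since the article gives none. Cells show mean Tau before and after correction, and the share of children significant after correction.

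| Natural gain | nB = 25 | nB = 75 |
|---|---|---|
| 0.02 SD per report (0.06 per week) | 0.172 → 0.169; 22% | 0.418 → 0.417; 46% |
| 0.05 SD per report (0.15 per week) | 0.402 → 0.396; 39% | 0.737 → 0.734; 93% |
| 0.10 SD per report (0.30 per week) | 0.669 → 0.655; 75% | 0.886 → 0.881; 100% |

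The correction never moves mean Tau by more than 0.014. The percentages also include the inflation from autocorrelation in step 5. With independent data the first row gives 9% and 39%.

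**5. False positives without trend or effect (simulation, 30,000 AR(1) series; baseline-corrected Tau-U, usual standard error).**

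| Autocorrelation | nB = 25 | nB = 75 |
|---|---|---|
| 0 | 5.1% | 4.6% |
| 0.2 | 9.9% | 10.1% |
| 0.4 | 17.4% | 16.5% |
| 0.6 | 27.4% | 27.4% |

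Variants at autocorrelation 0.4, for nB = 25 and 75 in that order:
- No trend correction: 16.4% and 16.8%.
- Standard error widened for the variance of S_A: 16.2% and 16.5%.
- The full form that also adds the treatment-phase trend: 17.8% and 19.2%.
- Rounded sum scores in place of continuous scores: 16.9% and 16.4%.
- One-sided 5%: about 13%.
- Five-report phase with the widened standard error: 11.6%.

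The true standard deviation is about 1.38 times the nominal one. Summing z over 15 children and dividing by √15 leaves 16.8% and 14.2%, because every child's standard error is too small by a similar factor.

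**The case against.** The strongest reply is that Tau-U is not the plan's test. It is an additional effect size, and the sentence on testing describes what the method can do. The committed within-child test and the basis for power is the PDT, which is said to handle autocorrelation, and the group effect is built from individual p-values. This stands. A reader might infer that the primary analysis itself runs at 16–18% false positives. The documents do not support that, since the figure holds only if Tau-U is tested or pooled with a standard error that the article never names.

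A reader might also take 0.033 as the general ceiling on the correction. It is the ceiling only when phases B, C and D are pooled, while Section 3.1.1 describes Tau-U between two phases. The correction reaches 0.50 at the five-report minimum.

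The trend sizes in step 4 are undocumented. A gain of 0.06 SD a week over the 13.5 weeks between the baseline midpoint and the midpoint of all treatment is 0.81 SD, about the whole planned effect. For baseline against a 25-report phase it is 0.31 SD. The percentages are therefore illustrations, but the ceiling in step 2 does not depend on them.

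Visual analysis also examines trend, so it is too strong to say that an improving child will necessarily be credited with a treatment effect. For the baseline, however, visual analysis rests on the same 6 reports per informant.

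Finally, a multilevel piecewise model would not rescue the design. At autocorrelation 0.4 the baseline slope from 6 reports has a standard error of about 0.82 SD per week per child, and about 0.82/√15 = 0.21 if 15 children share one slope. Extrapolated over 13.5 weeks this is about 2.8 SD. The two-week baseline is the real constraint, which argues against replacing the PDT with such a model.

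**Conclusion.** The statement that Tau-U can control baseline trends is wrong for this design. Against phases of realistic length the correction is capped at 0.10 (25 reports, equal split assumed) or 0.033 (75 reports), and a continuing trend passes through almost untouched. This follows from the reporting schedule alone.

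The inflation is conditional. If Tau-U is tested with its usual standard error, a two-sided 5% test has about 16–18% false positives per child and about 14–17% pooled at autocorrelation 0.4. Across autocorrelations of 0.2 to 0.6 the per-child rate is about 10% to 27%. It rests on AR(1) errors and an assumed α of 0.05.

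Neither result shows that the PDT is inflated in this way. As described, though, the PDT compares medians without a stated trend adjustment, so no statistical method in the analysis of the frequent measure effectively controls baseline trend. This should be fixed. It corrects a claim and closes off an unsuitable use of Tau-U, and it does not invalidate the committed test.

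**What to change.** - In Section 3.1.1, delete the claim that Tau-U controls baseline trends, and state that 6 baseline reports allow almost no trend correction.
- Report Tau or Tau-U as a descriptive non-overlap size, with an interval from a block or AR(1) bootstrap.
- State that the standard Tau-U z-test and its inverse-variance weights will not be used for individual or group inference, and that the group p-value in Section 3.1 comes from the PDT.
- Add to Section 4.1 (Strengths and limitations) that improvement already under way before treatment cannot be separated from a treatment effect.
- Optionally, add a multilevel piecewise AR(1) model as a sensitivity analysis, noting how imprecise its baseline slope will be.

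The cost is a few changed sentences, a little programming, wider intervals and a weaker stated claim. No change to data collection is needed.

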### Assessments

2.3

Parents and teachers report on the ESM measures using the M-path smartphone application three times a week (Monday, Wednesday and Friday) for the entire study duration.

Supplementary clinical and standardized assessments will be administered online. Both parents are invited to fill out the questionnaires. If it is not feasible for both parents to participate, the parent who spends the most time with the child will be asked to complete the questionnaires. At baseline [T0], a comprehensive clinical assessment will be conducted to evaluate the primary study outcome, as well as relevant predictors, covariates, and potential confounding factors (see Table 2, for an overview). At the start of each new study phase [T1, T2, and T3], parents and teachers will report only on SM symptoms. At post-treatment [T4] and follow-up [T5], parents and teachers will report on both SM symptoms and confounding factors. A clinical interview with parents will be conducted during the pre-treatment, post-treatment, and follow-up assessments.

**Table 2 tbl2:** Overview of assessments and informants.

Instrument	Variable	Moment of assessment					
		T0	T1	T2	T3	T4	T5
*Primary outcomes*							
Selective Mutism Questionnaire (SMQ-NL)	SM symptoms	P	P	P	P	P	P
Social Context of Speaking (SCS)	SM symptoms	T	T	T	T	T	T

*Secondary outcomes*							
Child Behavior Checklist (CBCL)	Behavioral and emotional problems	P				P	P
Teacher Report Form (TRF)	Behavioral and emotional problems	T				T	T
Structured Clinical Interview for DSM-5 disorders in children and adolescents (SCID-5 Junior)	DSM-5 classification of disorders	P				P^a^	P^a^
Fear Survey Schedule for Children Revised (FSSCR)	Anxiety symptoms	C				C	C
Parenting Burden Questionnaire (Opvoedingsbelangsting vragenlijst: OBVL)	Parenting burden	P				P	P
Clinical Global Impression Scale – Improvement	Severity of psychopathology		Th	Th	Th		
Child Observation Rating Scale	Overall Well-Being		C	C	C		
Visual Facial Anxiety Scale (VFAS)	Level of Anxiety		C	C	C		
Family Accommodation Scale (FASA)	Family accommodation	P				P	P
Virtual reality evaluation	Evaluation of VR		P	P	P	P	

*Predictors*							
Adult Self Report (ASR)	Adult problem behavior	P					
PABI	Parenting style	P					
Immersive tendencies – Parent version	Immersive tendencies	P					
Vineland-3-NL for parents	Adaptive functioning	P					
Vineland-3-NL for teachers	Adaptive functioning	T					
Demographic variables	Demographics	P					

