#### Secondary outcomes

3.1.2

*Standardized assessment:* Overall well-being (CORS) and severity of psychopathology (CGI) will be plotted against time and will be subjected to visual inspection for upward and downward patterns. A Kendall's Tau correlation [54] will computed to evaluate whether there is a significant upward or downward trend in overall well-being or CGI scores during treatment.

The secondary outcomes changes in symptoms of anxiety (FSSCR), and psychological functioning (CBCL, TRF) between the baseline assessment, post-intervention assessment and follow-up assessment will be subjected to formal testing. These secondary outcomes are selected because they provide theoretically relevant validation and interpretation of the primary outcome measure. These outcomes will be evaluated by calculating an RCI. Friedman's ANOVA will be used to test for differences on a group level. Due to the risk of increased Type I error, appropriate correction methods for multiple comparisons where relevant (e.g., Benjamini–Hochberg) will be applied.

The remaining secondary measures, parenting burden (OBVL) and family accommodation (FASA), will be analyzed descriptively and treated as exploratory as these outcomes help to better understand the family system and how these factors may be associated with potential treatment effects. This approach allows us to maintain rigor in the interpretation of the primary endpoints, while using the secondary outcomes mainly to contextualize, validate, and deepen the understanding of the primary effects.

*Qualitative interview:* The qualitative data from the VR user experience evaluation will be examined using deductive thematic analysis to uncover and interpret key themes [55]. Qualitative interviews will complement the quantitative measures by providing insight into treatment acceptability and user experiences. These findings will help contextualize the quantitative outcomes and contribute to evaluating the feasibility of the intervention and the perceived role of VRET within the broader treatment. Feedback on the VRET application will also be collected to guide future improvements.

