#### Handling of missing data

3.1.4

In single-case experimental designs (SCEDs), missing observations are not imputed for the purposes of visual analysis. Missing data points are displayed as gaps in the time series, allowing us to interpret potential patterns of missingness and to examine whether they may relate to the dependent variables or to contextual factors [56]. This is consistent with standard SCED methodology, in which transparency of the raw observation stream is essential for evaluating within-person change. For the statistical analyses, missing values will be handled differently. Because inferential SCED analyses require a complete time series within each participant, within-person imputation procedures will be applied.

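### Friedman's ANOVA, the named group test for the questionnaires, cannot use a child with a missing wave although the plan expects missing data, and a drop-in test for incomplete data exists

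*Protocol article*

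**What the plan says.** In the protocol article, Primary outcomes (3.1.1) gives the group test for SMQ-NL (parent) and SCS (teacher): "To test for differences on a group level Friedman's analysis of variance (ANOVA) [53] will be used". Secondary outcomes (3.1.2) repeats it for FSSCR, CBCL and TRF at baseline, post-treatment and follow-up: "Friedman's ANOVA will be used to test for differences on a group level".

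The waves that enter the SMQ-NL and SCS test are not listed. Table 2 schedules both scales at T0, T1, T2, T3, T4 and T5. The Assessments section (2.3) agrees. It places the primary outcome in the baseline assessment, and for the three middle waves it says: "At the start of each new study phase [T1, T2, and T3], parents and teachers will report only on SM symptoms". The same symptom reports are then repeated after treatment and at follow-up. T2 falls after completion of step 5 and T3 after completion of step 10.

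The sample size section (3.1) gives the reason for enrolling 15 children: "To account for potentially higher dropout rates and missing data". It states no rate. Handling of missing data (3.1.4) leaves gaps in the graphs and then says, for statistical analyses: "Because inferential SCED analyses require a complete time series within each participant, within-person imputation procedures will be applied".

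Table 2 lists the two scales under primary outcomes, but 3.1.1 gives them a supporting role: "These questionnaires serve to validate the results obtained from the frequent measurements".

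**The concern.** The standard Friedman test ranks each child's scores across all waves entered. A child lacking one of those scores has no complete set of ranks and contributes nothing, including the scores already collected. The plan foresees missing data and names a test that cannot use the children affected.

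The imputation rule does not clearly help. Its stated reason is that inferential single-case analyses need a complete time series, which describes a diary of about 117 points per child. If it were stretched to the questionnaires, a dropout's T4 and T5 would be built from that child's two to four earlier scores. That would supply by assumption the change the test is meant to detect.

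There is also a selection issue. Because T2 and T3 are tied to completing steps 5 and 10, a child whose progress stalls may never produce them. If those waves enter the test, complete sets may over-represent children who progressed.

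**Working it through.** **The plan's own figure.** The only power statement (3.1) is that four to eight children suffice at d = 0.8 and autocorrelation 0.4. It concerns pooled single-case p-values, not Friedman's test. An approximate simulation of a median-difference test, calibrated for autocorrelation and pooled at 0.05, gives one-sided power of 0.71-0.80 with 4 children and 0.93-0.97 with 8. Two-sided per-child p-values give 0.42-0.51 and 0.61-0.73. Alpha, sidedness and target power are not stated, so the figure is plausible one-sided but can be neither confirmed nor refuted. The plan states no power for Friedman's test.

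**Complete sets under isolated gaps.** From the document: 15 children, and six waves (SMQ-NL, SCS) or three (FSSCR, CBCL, TRF). Assumed: each assessment is missed independently with probability q. Expected complete sets = 15 × (1 − q)^k.
- k = 6: q = 5% gives 15 × 0.95^6 = 11.0; q = 10% gives 15 × 0.90^6 = 8.0.
- k = 3: q = 5% gives 15 × 0.95^3 = 12.9; q = 10% gives 15 × 0.90^3 = 10.9.

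**Power with six waves.** All of the following is assumed: gain of 0.8 between-child SD by T4; within-child SD 0.6, which implies a correlation of 1/(1 + 0.36) = 0.74; dropout starting at T2-T4; missed assessments after T0; missingness unrelated to the scores; test at 0.05; 1,500 runs per scenario.

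| Dropout / missed per wave | Mean complete sets | Friedman | Skillings-Mack | Difference (points) |
|---|---|---|---|---|
| none / none | 15 | 0.97 | 0.97 | 0 |
| 20% / 5% | 9.2 | 0.74 | 0.87 | 13 |
| 30% / 5% | 8.1 | 0.67 | 0.84 | 17 |
| 20% / 10% | 7.0 | 0.59 | 0.87 | 28 |
| 30% / 10% | 6.2 | 0.51 | 0.81 | 30 |

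Independent repeats agree within a few points. The mildest of the four missing-data scenarios gave 0.75 vs 0.88 and 0.78 vs 0.88 (13 and 10 points). The harshest gave 0.49 vs 0.80 and 0.52 vs 0.79 (31 and 27 points). Null rejection for Skillings-Mack was 0.036-0.053 here and up to about 0.07 in a repeat.

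**Dropout alone.** With 20% dropout and no isolated gaps, the gain under the same assumptions is about 1-2 points.

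**Lower correlation, dropout only.** With a within-child correlation of 0.5 and 2,500 runs, Friedman vs Skillings-Mack is:

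| Dropouts of 15 | Gradual change | Step change |
|---|---|---|
| 0 | 0.87 vs 0.87 | 0.94 vs 0.94 |
| 3 | 0.77 vs 0.81 | 0.87 vs 0.91 |
| 5 | 0.66 vs 0.74 | 0.78 vs 0.88 |
| 7 | 0.52 vs 0.65 | 0.64 vs 0.85 |

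At correlation 0.7 with 3 dropouts, the figures are 0.95 vs 0.96 (gradual) and 0.98 vs 0.99 (step).

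**Three waves.** The gain is about 2-11 points. It is smaller because a child who leaves before T4 has only T0, and neither test can use a single score.

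**The case against.** A reader might infer that the plan deletes dropouts from a T0-T5 analysis and that power therefore collapses. The document does not support that.
- The six-wave set is inferred from Table 2. With fewer waves, fewer children are lost.
- Deletion is the test's default behaviour, not a stated rule. The sentence on statistical analyses in 3.1.4 could be read as covering the questionnaires.
- The size of any loss rests on dropout, gap and correlation values that the article does not give. Much of it is unavoidable: Skillings-Mack itself falls from 0.97 to 0.81-0.87 in the six-wave table.
- The test supports the diary analysis, and no power is claimed for it.

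There are also safeguards. Questionnaires are online, both parents are invited and one suffices, and the researcher contacts families monthly. Headset discomfort need not end school treatment or questionnaire completion. Finally, an article may leave missing-data detail to a fuller document.

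All of this stands as a limit on size and severity. It does not remove the point. The article does choose the test, and that choice fits poorly with missingness the article itself expects. The second-parent provision does not cover SCS, which has a teacher as its informant.

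**Conclusion.** The concern holds in a limited form. Friedman's test cannot use a child with a missing wave, missing data are expected, and the imputation rule is justified only for the diary series.

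The benefit of changing the test ranges from about 1-2 points of power (20% dropout, high within-child correlation, no isolated gaps) to roughly 10-30 points (20-30% dropout plus 5-10% missed assessments per wave), and is about 2-11 points for the three-wave outcomes. These figures rest on assumed inputs and on missingness unrelated to the scores.

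No stated figure is contradicted, and the main diary analysis is unaffected. The possible tilt towards children who progressed follows from how T2 and T3 are defined. It is a plausible risk that has not been quantified, and a different rank test would not cure it.

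**What to change.** 1. In 3.1.1, name the waves that enter the group test for SMQ-NL and SCS.
2. In 3.1.1 and 3.1.2, replace Friedman's ANOVA with the Skillings-Mack test. It is identical when data are complete and uses every child with at least two of the assessments tested.
3. In 3.1.4, state that the within-person imputation rule applies to the diary series and that questionnaire scores are not imputed by it.
4. Report reliable-change results as counts out of all enrolled children, with the number lacking T4 or T5 shown separately.

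The cost is analysis wording only; no data collection changes. The downside is a less familiar test that still assumes missingness is unrelated to the unseen scores. It therefore does not remove bias from informative dropout, and the report should say so.
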